## Abstract

**Background:**

The contribution of birth defects, including cleft lip and palate, to neonatal and infant mortality and morbidity is substantial. As other mortality and morbidity causes including infections, hygiene, prematurity, and nutrition are eradicated in less developed countries, the burden of birth defects will increase proportionally.

**Methods/Design:**

We are using cleft lip and palate as a sentinel birth defect to evaluate its burden on neonatal and infant health and to assess the effectiveness of systematic pediatric care during the first month and first two years of life in decreasing this burden. The neonatal intervention, consisting of weekly pediatric evaluation and referral to appropriate care, is delivered to about 696 infants born with cleft lip and/or palate in 47 hospitals in South America. Neonatal mortality in this group will be compared to that in a retrospective control group of about 464 infants born with cleft lip and/or palate in the same hospitals. The subgroup of infants with isolated clefts of both the lip and palate (about 264) is also randomized into two groups, intervened and non-intervened, and further followed up over 2 years. Intervened cases are evaluated by pediatricians every three months and referred for appropriate care. The intervened and non-intervened cases will be compared over study outcomes to evaluate the intervention effectiveness. Non-intervened cases are matched and compared to healthy controls to assess the burden of cleft lip and palate. Outcomes include child's neurological and physical development and family social and economic conditions.

**Discussion:**

Large-scale clinical trials to improve infant health in developing countries are commonly suggested, making it important to share the methods used in ongoing studies with other investigators implementing similar research. We describe here the content of our ongoing pediatric care study in South America. We hope that this may help researchers targeting this area to plan their studies more effectively and encourage the development of similar research efforts to target other birth defects or infant outcomes such as prematurity and low birth weight.

## Background

Neonatal and infant mortality and morbidity are high in less developed countries. Each year about 10 million children die worldwide, with extensive between and within country variation [1,2]. Almost half of these deaths (about 4 million) occur among newborns before one month of age [2-4]. The majority (about 95%) of all neonatal deaths occur in less developed countries, where 34 neonates die among every 1000 live births, compared to 5 neonates in developed countries [3,4]. In the past two decades, greater reductions have been observed in child mortality than in neonatal mortality with the lowest reductions observed in the early neonatal phase [4], leading to a greater number of deaths within the first month of life.

Among the main causes of neonatal mortality in developing countries (infections, prematurity complications, and birth asphyxia), congenital anomalies constitute the fourth leading cause, and are responsible for about 7–10% and 3.8% of neonatal and under – 5 mortality, respectively [1,3,4]. Congenital malformations are increasingly contributing to overall infant mortality in developed countries such as the United States [5], where 20% of infant deaths in 2001 were related to congenital malformations [6]. The burden of birth defects will also be expected to increase in developing countries as public health, nutrition, and other primary health interventions succeed in reducing main mortality and morbidity causes such as infections and low birth weight. Besides mortality, birth defects also increase the risk for disability. In 2002, more than 27 million lost Disability Adjusted Life Years (DALYs) forming about 1.8% of the overall burden of disease were related to congenital abnormalities [1].

Oral clefts are common birth defects that affect about 1 in every 700 births with varying prevalence by population origin and socioeconomic status [7,8]. Cleft lip and palate occurs as both isolated and syndromic forms [9]. Isolated forms are unassociated with any other structural or cognitive birth defects. Syndromic forms of clefts have a wide range of etiologies with more than 400 reported in Online Mendelian Inherited Diseases in Man [10] from single gene causes and with other clefts occurring secondary to chromosomal anomalies, teratogenic exposures, and as sporadic disorders without recognized etiologies.

Isolated forms are readily targeted by care provided by multi-specialty teams yet may still have substantial infant morbidity and mortality specifically in cases with limited access to care that might include for example, education for appropriate feeding. Malnourishment of infants born with clefts because of feeding problems may enhance the impact of other mortality risk factors such as infections. A few studies have reported several-fold increased neonatal and infant mortality risks among infants born with clefts, specifically among syndromic forms [11-13]. Further, there is evidence of a long-term burden even of isolated forms, mainly in challenges for psychological and social adjustment [14-16] as well as reduced life expectancy [17].

Since clefts are readily apparent at birth, they can serve as sentinels for other birth defects and their impact. We are studying cleft lip and palate as a model birth defect to determine whether an increased pediatric care model can decrease mortality and morbidity in an infant population born in-hospital mainly to indigent populations in South America. The primary research aims include evaluating if neonatal mortality among children born with cleft lip and/or cleft palate can be decreased by a systematic pediatric intervention over the first month of life, and if systematic pediatric care over the first two years of life can improve the neurodevelopment and growth of children born with isolated forms of cleft lip with cleft palate compared to usual pediatric care. The neurodevelopment and growth of this latter group will also be compared to those of healthy control babies without birth defects receiving usual pediatric care. Secondary research aims include evaluating the effectiveness of the pediatric intervention and follow-up program on other neonatal and two-year of life health outcomes, which are described below in further detail.

The study benefits from a well-established consortium of pediatricians working under the auspices of the Estudio Colaborativo Latino Americano de Malformaciones Congenitas (ECLAMC), a birth defects surveillance program that has been active in South America since 1967 [18]. Currently, about 80 hospitals are enrolled in ECLAMC and carry out surveillance of birth defects on approximately 200,000 births per year. We used this infrastructure to identify pediatricians who could provide direct care to infants born with cleft lip and palate and follow them closely for the first month to ensure that appropriate medical and surgical interventions were undertaken. The impact of systematic pediatric care throughout the first two years of life on health is also being studied in the subgroup with isolated cleft lip and cleft palate using the same infrastructure.

The objectives of this paper include reporting how the project was established and describing study design and interventions. There has been increased emphasis recently for establishing large-scale clinical trials to study perinatal and neonatal health interventions in less developed countries. Recent study reviews have identified the need for more clinical trials to address several research gaps in the provision of neonatal care in these settings [19,20]. Further evaluation of the effectiveness of alternative models for neonatal care content and delivery is one emphasized theme. Yet little empirical guidance on how to optimally design and implement these trials in less developed countries is available. As more resources are being allocated into this field, it is important to share methods of ongoing large-scale interventional trials. This may help researchers plan their studies to appropriately adjust interventions, improve procedures, and estimate adequate budgets. We hope that sharing our study methods would be of direct relevance to researchers and funding agencies targeting this area.

## Methods/Design

### Setting and participants

Study participants are being recruited in 47 ECLAMC hospitals from 35 cities in Argentina, Brazil, Bolivia, Chile, Colombia, Ecuador and Venezuela (see list in acknowledgements section). Study participants include live born infants with cleft lip and/or palate and healthy infants and their parents. Infants with a typical oral cleft as the only detected congenital anomaly are considered isolated cases. Infants with atypical oral clefts (oblique facial clefts, congenital healed clefts, midline cleft lip, submucous cleft palate, bifid uvula) are excluded. In this study, syndromic forms of cleft lip and palate include cases with recognized syndromes, cases with chromosome abnormalities, cases with one or more major structural anomalies other than cleft lip and palate, cases with cognitive delay (IQ or equivalent less than 80), or cases exposed to recognized teratogens in utero (phenytoin or valproic acid). Cases born to mothers who smoked or used alcohol during pregnancy who otherwise do not meet the syndromic form criteria listed above are considered isolated cases. Syndromes are classified using chromosomal analysis and/or by physical findings, and all cases are reviewed by at least two experienced dysmorphologists [[name], [name], [name], [name], [name]].

#### Inclusion/exclusion criteria

The neonatal prospective group that receives the pediatric intervention includes infants born with typical clefts of any etiology or affected segment (lip, gum, hard palate, soft palate) in participating hospitals between January, 2003 and December, 2005, and diagnosed as eligible within the first 48 hours after birth, with an initially projected total of about 696 cases to be available for recruitment. No other inclusion or exclusion criteria are imposed on this group. Since it was considered unethical to randomize neonatal subjects into treatment and no treatment control groups, as there was a strong sentiment that the intervention forms the current standard of care in the United States, a retrospective control group born in 2001 and 2002 with clefts in the same hospitals was chosen. This control group is projected to include about 464 cases, yet data are still being processed. This group of infants had previously received routine pediatric and medical care offered by their communities during the neonatal period. A schema of the study design is shown in Figure 1.

**Figure 1 F1:**
[figure not shown]
**Study Design**. Figure 1 presents a flowchart of the study design of the neonatal and the two-year subprojects. All infants born with a typical form of cleft lip and palate in the study hospitals are enrolled in the neonatal subproject. Only isolated cases with both cleft of lip and cleft palate who are singleton births, normal birth weight, and without complications other than cleft lip and palate that require systematic care are enrolled at birth in the two-year subproject and randomized into intervened and non-intervened groups. A group of healthy controls is matched to the non-intervened group by gender, date and hospital of birth at a ratio of 2 to 1. A = Evaluating the impact of the intervention on neonatal mortality. B1 = Evaluating the impacts of cleft lip and palate on child's development and family socioeconomic outcomes (Two-year subproject). B2 = Evaluating the impact of the two-year intervention on child development and family socioeconomic outcomes.

The two-year study group includes children from the neonatal prospective subgroup who are born with isolated forms of both cleft lip and cleft palate. Children with syndromic forms are excluded, as are twins and children with birth weight less than 2500 grams or who have complications other than cleft lip and palate that require systematic care. A group of healthy controls born without birth defects and subject to the same exclusion criteria and whose gestational age is between 37 and 42 weeks are also included in the two-year study.

### Neonatal intervention

The neonatal intervention in the prospective group involves weekly monitoring and evaluation of infant health through follow up visits to participating ECLAMC pediatricians. The visits usually occur at the hospital of birth or private offices of participating pediatricians; visits to subjects' homes are encouraged when the weekly visits are missed. During each of the four neonatal visits extending to one month of age, the pediatrician conducts a clinical assessment of infant health and growth. Special emphasis is placed on weight gain, feeding problems, and medical complications such as hyperbilirubinemia or infection. The pediatrician also interviews parents for family and household factors that may affect the infant health. Based on assessment results, the pediatrician refers the infant to appropriate health professionals for specialized care. Recommendations and instructions to parents regarding infant needs and optimal care are also provided. If the child demonstrates a failure to gain weight, physicians will, using standard medical judgment, determine whether hospital admission is appropriate or whether the child can be sent home. If sent home, the infant may be followed at more frequent intervals depending on the severity of the weight loss or other medical complications. Any decrease in weight by greater than 10 percent will require hospital admission and weight decreases between 0 and 10 percent will have suitability for admission determined by the referring physician.

The impact of the pediatric intervention on neonatal mortality will be assessed by comparing mortality rates between the retrospective and prospective study groups. Birth time periods for the two groups are close and consecutive, limiting time changes in conditions such as quality of health care that may affect mortality and confound the evaluation of the intervention's impact.

ECLAMC started in 2001 a program titled "ORIENT" to provide guidance prior to hospital discharge to parents of infants born with birth defects about appropriate care and available treatments for the infant [18]. The retrospective group has also received this standard of care available at ECLAMC hospitals in addition to the standard of care available in the community.

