### Study outcomes

The neonatal outcomes include overall mortality at 28 days of life (primary outcome), mortality in subgroups of isolated and non-isolated cleft groups, hospitalization days, and refinement of syndromic classification in the retrospective group. The impact of the neonatal intervention on infant mortality will also be evaluated and phone interviews are conducted with parents of prospective and retrospective groups when needed to inquire about child's survival at one year of age. The primary outcomes of the two-year study include overall neurodevelopment (measured by BINS) and weight changes. Secondary outcomes include performance on four ability areas including neurological functions/intactness, receptive functions, expressive functions, and cognitive processes (measured by the BINS), speech (measured by REEL), height changes, hearing, timing of cleft surgery, mortality, refinement in syndromic status classification, and emotional, social, and economic performance of the family.

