### Power analysis

The power analyses prepared prior to study initiation are reported in Tables 1 and 2 for the neonatal and the two-year subprojects respectively. The power estimation for the primary hypothesis of reduction in neonatal mortality in the prospective group compared to the retrospective control group assumes a simple random sample scheme and a probability of Type I error of 0.05. Power is estimated for alternative neonatal mortality rates in both the prospective and retrospective control groups due to the lack of robust estimates at the time of study initiation of baseline mortality rates in the retrospective group and of potential achievable reductions in neonatal mortality due to the intervention. Mortality rates of 20, 25, and 30% are assumed for the retrospective group. The neonatal mortality rate in the prospective group is also assumed to not exceed 25% and to be not higher than that of the retrospective group (one-sided test). The power calculation for the neonatal subproject is based on a sample size of 464 cases in the retrospective group and 696 cases in the prospective group. This analysis shows that acceptable power (>0.7) is available for reductions of about 30% or more in assumed baseline neonatal mortality rates (See Table 1).

**Table 1 T1:** Power to Detect Differences in Neonatal Mortality Proportions

*Neonatal Mortality in Retrospective Group*	*Neonatal Mortality in Prospective Group*	*Power*
0.20	0.12	0.97
	0.15	0.68
	0.17	0.34
0.25	0.15	0.99
	0.17	0.94
	0.20	0.61
	0.22	0.30
0.30	0.15	>0.99
	0.17	>0.99
	0.2	>0.99
	0.22	0.98

**Table 2 T2:** Power to Detect Differences in Means of Continuous Outcomes in the Two-Year Study

Sample Size per Group	Standardized Effect Size			
	0.15	0.25	0.4	0.5
60	0.30	0.60	0.92	0.98
90	0.40	0.76	0.98	>0.99
120	0.49	0.85	>0.99	>0.99
150	0.55	0.91	>0.99	>0.99
160	0.59	0.93	>0.99	>0.99
170	0.61	0.94	>0.99	>0.99

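### Raw hospitalization days cannot be read as benefit or harm: death truncates them, and the intervention itself orders some of the admissions they count

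*Protocol article*

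**What the plan says.** Study outcomes (protocol article) names the primary neonatal outcome, "overall mortality at 28 days of life (primary outcome"), and then lists "mortality in subgroups of isolated and non-isolated cleft groups, hospitalization days, and refinement of syndromic classification in the retrospective group". The Background section presents the secondary aims as tests of whether the programme works on further health outcomes. Statistical analysis says that effects on the studied outcomes will be assessed by comparing intervened and control groups. Hospitalization days is thus a comparative outcome. The article states no preferred direction for it.

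Neonatal intervention describes what only the prospective group receives: "The neonatal intervention in the prospective group involves weekly monitoring and evaluation of infant health", over four visits in the first month with emphasis on weight gain. Two admission provisions follow. The first is mandatory: "Any decrease in weight by greater than 10 percent will require hospital admission". The second covers smaller losses and leaves the decision to clinical discretion: "weight decreases between 0 and 10 percent will have suitability for admission determined by the referring physician". For the retrospective group, Inclusion/exclusion criteria says: "This group of infants had previously received routine pediatric and medical care offered by their communities during the neonatal period".

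Power analysis sets the mortality scenarios: "Mortality rates of 20, 25, and 30% are assumed for the retrospective group". The prospective rate "is also assumed to not exceed 25% and to be not higher than that of the retrospective group (one-sided test"). Table 1 uses 12 to 22% for the prospective group.

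**The concern.** Two features make the count hard to interpret.

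1. **Truncation by death.** An infant who dies early can accrue only a few hospital days. If the primary hypothesis is true, the groups differ in how many infants live long enough to accrue days, so the outcome moves with mortality as well as with morbidity.
2. **The intervention orders part of what is counted.** Weekly weight checks and a weight-based admission rule apply in one group only. Some prospective hospital days are the intervention being carried out.

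At stake is the reading of this outcome. A rise could reflect survival and ordered admissions. A fall could reflect averted illness, or infants dying before they accrue days.

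**Working it through.** The article gives no figure for hospitalization days, so there is none to reproduce. The check asks how far, and in which direction, the two features can move the mean.

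**Inputs from the article**
- Group sizes: 464 retrospective, 696 prospective (Power analysis).
- Mortality: 20% versus 15%, a row of Table 1. With these sizes, a one-sided 0.05 test and a continuity correction, power is 0.687 against the stated 0.68, so the inputs are read as the authors used them.
- Expected deaths in the retrospective group: 464 x 0.20 = 93, 464 x 0.25 = 116, 464 x 0.30 = 139. Truncation is not a rare event under these scenarios.

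**Assumptions (not in the article)**
- Survivor stay s: 3 to 8 days.
- Hospital days of a dying infant d: 1 to 10.
- Stay of an infant whose death is averted g: equal to s, or 14 days.
- Net extra admissions beyond what routine care would have made: 0 to 10% of infants, 5 days each.
- Stays averted by better feeding or earlier referral: up to 10% of infants, 7 days each.

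**Formula**

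Shift in mean hospital days = (pR - pP) x (g - d) + (net extra share x 5) - (averted share x 7), where pR and pP are retrospective and prospective mortality.

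| Component | Calculation | Shift, days per infant |
|---|---|---|
| Truncation, g = s = 3, d = 10 | 0.05 x (3 - 10) | -0.35 |
| Truncation, g = s = d | 0.05 x 0 | 0 |
| Truncation, g = s = 8, d = 1 | 0.05 x (8 - 1) | +0.35 |
| Truncation, g = 14, d = 10 | 0.05 x (14 - 10) | +0.20 |
| Truncation, g = 14, d = 1 | 0.05 x (14 - 1) | +0.65 |
| Net extra ordered admissions, 5% | 0.05 x 5 | +0.25 |
| Net extra ordered admissions, 10% | 0.10 x 5 | +0.50 |
| Averted stays, 10% | -0.10 x 7 | -0.70 |

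The extremes combine to -0.35 - 0.70 = -1.05 and +0.65 + 0.50 = +1.15 days. With no averted stays, most combinations are positive. Once averted stays are allowed, the sign depends on quantities the article does not give. Every row assumes the same reduction in mortality, so the same survival benefit can appear as more days, fewer days or no difference.

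**The alternative measure.** For days alive and out of hospital to day 28, averting one death adds 28 - g - h, where h is the days that infant would have lived outside hospital before dying. If dying infants spend all their days in hospital (h = 0), the survival part is 0.05 x (28 - 14) = +0.70 for g = 14, and 0.05 x (28 - 3) = +1.25 for g = 3. It stays positive unless g + h exceeds 28. Net extra admissions subtract up to 0.50 and averted stays add up to 0.70. Each component now has a direction that can be interpreted.

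**The case against.** The strongest reply has five parts.

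- **A reader might infer that an effective intervention must score as worse.** The article does not support this. It never says that fewer days is better, and the sign is not fixed: averted stays can outweigh ordered ones, and preventing deaths that follow long stays lowers the count. This objection stands, and the point is limited to uninterpretability.
- **A reader might infer that ordered admissions have no counterpart in 2001-2002.** Nothing says that control infants with similar weight loss were not admitted under routine care in the same hospitals. Only the net excess matters, and its size is unknown. This stands.
- **The counting window and the handling of deaths may be set out in the full protocol or analysis plan.** That is so, and their absence from an article is not held against it. The point rests on what the article does state: the choice of outcome, the one-sided admission rule and the assumed mortality.
- **The 20 to 30% rates are power scenarios, chosen for want of robust estimates.** This stands. The truncation component scales with the mortality difference and would shrink with it.
- **Days alive and out of hospital still counts ordered admissions.** It does, and it should: they are part of the policy's total effect. Removing them from the prospective group alone, while similar control admissions stayed in, would bias the comparison in favour of the intervention.

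The outcome is also not primary, and mortality is reported for the same infants, so an alert reader could set the two side by side. That limits the consequence but does not give the raw count a meaning.

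**Conclusion.** The point holds in a limited form. Raw hospitalization days, compared between the groups, mix truncation by death, intervention delivery and any true change in morbidity, so neither a rise nor a fall supports a conclusion about benefit. At 20% versus 15% mortality the separate components run from about -0.70 to +0.65 day per infant. Lengths of stay, net extra admissions and averted stays are all assumed, so this range shows that the sign is open and does not estimate the bias. The primary mortality comparison and the sample size are untouched. This is a worthwhile, inexpensive improvement to a non-primary outcome.

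**What to change.** 1. Make the comparative outcome days alive and out of hospital from birth to day 28, with zero days counted after death and all admissions counted identically in both groups.
2. Show 28-day mortality, birth stay and readmission days beside it, by group.
3. Keep raw hospital days as a descriptive measure of resource use.
4. Admissions triggered by the weight criterion may be tabulated for the prospective group to describe intervention delivery, but they must not be removed from the comparison.

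**Cost.** A change of outcome wording and one derived variable: days alive to day 28 minus hospital days in that window. The Cox model for mortality already needs the date of death. Separating the birth stay from readmissions needs admission and discharge dates. The article does not say whether these are captured for the retrospective group, whose data come from record abstraction and parent interviews, so this should be checked first. The main downside is that the measure mixes survival with hospital stay, which is why its components must be shown. No change to the clinical admission rule is implied.
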